## Abstract

**Background:**

The postmenopausal period can represent an opportunity for women to improve their health and well-being. The Active and Healthy Ageing in Women during early postmenopause (AHAWOMEN) study aims to identify the key determinants of an active lifestyle among middle-aged women, with a focus on the stages and the social-cognitive variables outlined in the Health Action Process Approach (HAPA) model, a theoretical framework for understanding health behaviour change. We expected that HAPA factors and processes of intention creation (motivational phase) and action adoption (volitional phase) will be significant predictors of exercise initiation and maintenance, supporting both the HAPA tenets and the efficacy of HAPA-based interventions.

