To test the HAPA tenets in middle-aged postmenopausal women while filling the abovementioned gaps in the literature, the main aim of this study is two-fold. First, we aim to explore the influence of the social-cognitive variables relevant at each stage of the process of behavioural change based on HAPA predictions, and second, to test the goodness of fit of the model for exercise behaviour among women in early postmenopause (up to ten years after menopause). Specifically, the sub-aims of the present study protocol are the following:To explore the HAPA constructs at every stage of the change process in new exercisers, that is participants adhering to exercise practice while simultaneously receiving an intervention based on the HAPA model (Intervention group). These will be compared with regularly active (active control) and non-active (sedentary control) postmenopausal women, all with different socio-demographic, personal and clinical characteristics. Consequently, this sub-aim has the following specific objectives:to determine changes in the HAPA variables in the intervention group throughout the study phases, and in this regard:H1: we hypothesise that there will be a significant improvement in both intentional-motivational and postintentional-volitional variables in the participants in the exercise programme supplemented with the HAPA intervention.to compare the intervention, sedentary and active groups across the motivational and volitional phases of the HAPA model, and in this regard:H2: we hypothesise that, at baseline, non-active women (i.e., sedentary and intervention groups) will show similar HAPA determinants of exercise intention, while the active controls will obtain more positive results in the HAPA motivational constructs, andH3: we hypothesise that, at post-intervention and subsequent follow-ups, the new exercisers and the active women will show similar HAPA self-regulatory skills of the volitional-actional stage but will differ significantly from the sedentary women.To explore whether the HAPA constructs at the different stages of the process of behavioural change — i.e., non-intention, intention, action and disengagement — and phases of the process, that is, motivational (preintention) and volitional (intention-action-adherence), predict the adoption of exercise behaviour among postmenopausal women. In this regard:H4: we hypothesise that while the HAPA model will be applicable to this population, supporting its main predictions, adjustments in the model predictions will be necessary to optimise its explanatory power, considering the experiences, resources and opportunities of middle-aged women, andH5: personal (i.e., fitness status, physical and mental health status and sociodemographic variables) and clinical factors (i.e., menopausal manifestations and menopause-related quality of life) will intersect with HAPA variables in the prediction of exercise behaviour and behaviour change, supporting the existence of phenomena that are pertinent and exclusive of middle-aged women and are grounded in their experiences, realities and needs.

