### Intervention

A three-component intervention will be offered, which includes:

A multicomponent, supervised exercise programme with a 3-month (12 weeks) minimum duration will be offered to the intervention group. The exercise programme will consist of three 1-h weekly sessions on alternate days. Participants will be able to choose from several schedules available in both the morning and afternoon periods. The programme will be designed and implemented by experts in Exercise and Sport Sciences and Sport and Exercise Medicine, following international recommendations for exercise in middle-aged women [96, 97]. The programme will include training for aerobic cardiorespiratory fitness, muscle resistance, as well as other fitness functions including flexibility, coordination and balance. Hence, it will meet the required conditions in terms of activity type, duration, frequency and intensity parameters and principles and methodology of training for a healthy, safe, successful and enjoyable practice for adult women, thus being suited to their characteristics and needs for maximising benefits while minimising risks. The programme will be implemented in supervised group classes conducted in a gym facility (e.g., in the university campus). To assess adherence to the programme, objective tracking measures will be utilised, including attendance monitoring. All these features are designed to optimise participation as well as outcomes. Additionally, a health insurance policy will be put in place to cover any potential risks and provide necessary medical assistance if required.A simultaneous intervention focusing on self-management of behavioural change, based on the tenets of the HAPA model, will be offered throughout the duration of the exercise programme. This intervention has been designed based on previous HAPA-based interventions [98–103]. To summarise, the intervention will provide information on the benefits of an active lifestyle and exercise, specifically for postmenopausal women, addressing risk perceptions and outcome expectations while facilitating the creation of an intention (Session 1). The participants will be also educated on the key factors for adopting and maintaining an active behaviour, such as identifying barriers and facilitators, basic self-monitoring and self-management skills for action regulation (e.g., self-monitoring, self-reinforcement, setting a daily time schedule, emotional regulation, seeking social support and reinforcement from significant others); these elements contribute to improving motivational action self-efficacy (Session 2). The subsequent 3 to 5 sessions will focus on motivational determinants of exercise initiation, including goal setting (behavioural intention), action planning and pre-actional/task self-efficacy to improve motivation and action initiation. Sessions 6 to 9 will address volitional determinants of maintaining adherence, covering self-regulatory skills including action and maintenance plans for autonomous exercise, maintenance and coping self-efficacy and relapse management (i.e., risk identification, functional responses and coping skills training). A final session is devoted to summarising the personal progress of the participants with this intervention. The aim of this intervention is to ensure that women not only adhere to the supervised exercise programme offered within the study, but mainly to promote long-term, self-managed adherence to the newly established lifestyle beyond the completion of the supervised exercise programme. To achieve this, the adherence promotion intervention will be delivered during the entire implementation of the exercise programme, divided into two phases according to the process of behavioural change. During the first phase of the programme, the focus will be on addressing issues pertaining to initiation and short-term maintenance. Researchers and implementers will play a central role in providing external regulation and support as a strategy to facilitate adherence. During the second phase of the programme, the emphasis will shift toward long-term maintenance. Building on the knowledge and skills acquired by the participants, the intervention will promote the transition to self-regulation and the development of intrinsic motivation based on enjoyment and personal growth.

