To address the first research question, exercise behaviour and HAPA constructs of the motivational and volitional phases (primary outcomes) will be compared across different phases (baseline, post-intervention and follow-ups) (H1) and between the different study groups (intervention participants, sedentary controls, active controls) (H2 and H3). Within-group and between-group analyses will be conducted using parametric (e.g., 1-way or 2-way ANOVAs, Student *t* test) or non-parametric tests (e.g., Friedman’s *χ*^*2*^ test and Wilcoxon’s *Z* pair comparisons for related samples, Kruskal–Wallis’ *H* test and Mann–Whitney’s *U* pair comparisons for independent samples). The choice of test will be determined by the compliance with parametric assumptions of normality and homoscedasticity. A calculation of the effect size will be also conducted (e.g., Cohen’s d). Covariates (e.g., age, menopausal symptom burden) will be introduced (e.g., ANCOVAs).

The second research question (H4 and H5) will be addressed using analyses of bivariate associations (e.g., Pearson *r*, Spearman *rho*), multiple linear regression analyses and multilevel clustering analyses to explore the correlates and predictors of outcome variables as well as intraindividual profiles or patterns of associations. Path analyses and analyses of indirect relationships between variables (e.g., mediation, moderation) will allow for a deep understanding of the complex associations between the study variables. Structural equation modelling will allow for testing the fit of data to the model based on HAPA predictions. Covariates will be introduced to control for their confounding effects (e.g., perceived health status). 

In addition, psychometric properties of the measures will be analysed (e.g., Cronbach’s *alpha*, intercorrelations).

A significance level of *p* < 0.05 will be established.

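### H1 is tested as before-after change within the intervention group; it should use the randomised sedentary arm, and any effectiveness conclusion should refer to the whole package

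*Protocol article*

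**What the plan says.** In *The AHAWOMEN project: aims and hypotheses*, the objective behind H1 is "to determine changes in the HAPA variables in the intervention group throughout the study phases". H1 then predicts that "there will be a significant improvement in both intentional-motivational and postintentional-volitional variables in the participants in the exercise programme supplemented with the HAPA intervention". No comparator is named.

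*Data management and analyses* calls exercise behaviour and the HAPA constructs the primary outcomes. It says that they "will be compared across different phases (baseline, post-intervention and follow-ups) (H1", and separately "between the different study groups (intervention participants, sedentary controls, active controls) (H2 and H3". H2 concerns baseline. H3 concerns levels after the intervention and at follow-up, across all three groups.

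The tests are given as examples: one- or two-way ANOVA and t tests, or rank-based alternatives. "The choice of test will be determined by the compliance with parametric assumptions of normality and homoscedasticity". On adjustment: "Covariates (e.g., age, menopausal symptom burden) will be introduced (e.g., ANCOVAs".

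*Procedures* states that non-active women are randomised to intervention or to a sedentary waiting-list control. *Measures* gives one schedule of six assessments.

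Under *Intervention*, "A three-component intervention will be offered": supervised exercise, HAPA sessions and health education. Sedentary controls receive neither of the first two and may take up the third voluntarily. The abstract expects HAPA factors and processes to predict exercise, "supporting both the HAPA tenets and the efficacy of HAPA-based interventions", and adds that the effectiveness of the model and of the intervention will be evaluated.

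**The concern.** H1 is a hypothesis of improvement on primary outcomes, but its assigned test looks only at the treated women. Anything that moves scores over time in both randomised arms then counts towards the programme. Three sources are plausible from the protocol itself:

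- Participants answer the same kinds of questionnaire at up to six assessments.
- They are self-referred volunteers willing to be randomised to an exercise programme.
- Baseline IPAQ serves both to assign women to study groups and to track activity afterwards, which invites regression to the mean in activity.

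The missing-data text justifies carrying control values forward on the ground that controls should not change. That presumes there is no drift, which is the very thing the randomised controls could check.

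A second issue concerns interpretation. Even a correct randomised contrast estimates the effect of exercise, HAPA sessions and health education together. Describing the result as efficacy of a HAPA-based intervention would go beyond what the arms can show.

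**Working it through.** **1. The plan's own figure.** *Participants and eligibility criteria* gives 80 per group for comparing means of independent groups, with alpha 0.05 and beta 0.2, inflated for 20% dropout: 80 / (1 − 0.20) = 100. This reproduces. The 80 cannot be recomputed because no mean difference or SD is printed. At two-sided 0.05 and 80% power it corresponds to d = (1.960 + 0.842) × √(2/80) = 0.443, compatible with the stated moderate effect. So the trial is sized for a comparison between groups, while H1 is a within-group test.

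**2. How often a within-arm test is significant with no intervention effect.** Inputs: n = 80 (document); drift δ in SD units shared by both arms and baseline to follow-up correlation r (both assumed); equal SDs at the two visits.

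- Standard error of mean change: √(2(1 − r)/80).
- P(significant) = Φ(δ/SE − 1.96) + Φ(−δ/SE − 1.96).
- Example, δ = 0.2 and r = 0.5: SE = √(1/80) = 0.1118; δ/SE = 1.789; Φ(−0.171) = 0.432, the second term being negligible.

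| Shared drift | r = 0.3 | r = 0.5 | r = 0.7 |
|---|---|---|---|
| 0.1 SD | 12% | 14% | 21% |
| 0.2 SD | 33% | 43% | 64% |
| 0.3 SD | 62% | 77% | 93% |

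In the contrast between randomised arms, the shared drift cancels and the error rate stays at 5%.

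**3. What baseline adjustment gains.** ANCOVA multiplies the outcome variance by 1 − r². For d = 0.443 at 80% power, the number per arm is 80 × (1 − r²): 73 (r = 0.3), 60 (r = 0.5), 41 (r = 0.7). With 80 evaluable per arm, power rises from 80% to about 84%, 90% and 97%. No extra participants are needed.

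**4. Where steps 2 and 3 apply.** The heading *HAPA constructs (all assessments)* suggests a full set at every visit, but the text beneath it splits the constructs.

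| Outcome | Described at baseline | Described afterwards |
|---|---|---|
| IPAQ activity | yes | yes |
| Intention | yes | yes, same measure |
| Outcome expectations | yes | yes, items reworded as perceived outcomes |
| Action and coping planning; maintenance and recovery self-efficacy | no | yes |

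For the last row no before-value is described. Before-after improvement cannot be tested there, and neither step 2 nor step 3 applies. The randomised comparison of post-intervention levels remains available.

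**5. Separating components.** Intervention arm: exercise, HAPA sessions and health education. Sedentary arm: health education if wanted. The arms differ by exercise and HAPA jointly, and no randomised arm receives exercise alone.

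**The case against.** The strongest reply is that the plan already holds a valid randomised comparison. H3 predicts that new exercisers will differ from sedentary women after the intervention, and those two groups are formed by randomisation. Comparing their post-intervention levels is not biased by season, repeat testing or regression to the mean, and omitting baseline costs precision only. This stands: a reader might infer that the trial has no controlled test, and that would be wrong. But H3 concerns volitional skills and is not linked to H1, whose test is fixed as comparison across phases.

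Several other stronger readings are tempting but not supported:

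- *Baseline adjustment and group-by-time tests are excluded.* The test and covariate lists are examples. Two-way ANOVA or ANCOVA could hold either term; they are simply not specified for H1.
- *Falling back on rank tests rules out comparing change between arms.* A Mann-Whitney test on change scores does that.
- *Covariates measured after baseline will be used.* The text does not say so, and perceived health status is named only for H4 and H5. Fixing covariates at baseline is a precaution.
- *H1 will be reported as efficacy of HAPA.* The abstract attaches its efficacy phrase to HAPA factors predicting exercise, and H1 names the exercise programme with its HAPA supplement. The link is an inference.
- *The package is dominated by supervised training.* At least 12 × 3 × 1 h = 36 h is contact time, not effect on planning or self-efficacy, which the HAPA sessions address directly.

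Bundling is also openly described. The interpretive point is therefore about wording, not a hidden design flaw.

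**Conclusion.** The point holds in a bounded form. The protocol assigns H1, on primary outcomes, to comparison across phases in the intervention group and leaves the randomised arm to other hypotheses. This is a stated choice, not detail left to an analysis plan. H1 could therefore succeed without any intervention effect: 33% to 64% of the time under a shared drift of 0.2 SD, and 12% to 93% over the wider grid of 0.1 to 0.3 SD. Drift and correlation are assumptions, and the figures apply only to outcomes measured before and after. The conclusion rests on the text and not on any particular value.

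For volitional constructs the difficulty is different: as described, an improvement has no starting value. No arm separates HAPA from exercise, so effectiveness conclusions reach only as far as the package.

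**What to change.** - Test H1 as the intervention-minus-sedentary difference at each post-baseline visit.
- Adjust for the outcome's own baseline value where one is measured: IPAQ activity, intention and, noting the reworded items, outcome expectations.
- Use baseline values of any other covariates, such as symptom burden.
- For planning and for maintenance and recovery self-efficacy, use the randomised post-intervention contrast and do not claim before-after improvement.
- Report within-arm change as description.
- Word the effectiveness statements in the abstract, and later conclusions, as the effect of exercise, HAPA sessions and health education together.

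The cost is some analysis work and a less HAPA-specific headline. It needs no new data or participants, and precision improves wherever baseline values exist.

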## Discussion

A recent study has concluded that Spain, which is currently the fourth longest-lived country in the world with a life expectancy of 83 years, will be ranked the highest in longevity in 2040, with a predicted increase of approximately 3 to 5 years of life expectancy, depending on living conditions and evolution of health indicators [1]. The study also highlights that the main causes of morbidity and premature death in the coming decades will be linked to non-communicable diseases, particularly those related to cardiovascular and metabolic disorders, overweight and obesity. Moreover, it is emphasised that lifestyle habits and inequalities related to health and disease processes will play a crucial role in shaping global health trends. In the most pessimistic scenarios predicted by the study, life expectancy could potentially decrease by almost half across all countries in the next generation. The findings of this study could potentially guide researchers, professionals and policymakers in making efforts aimed at improving health systems and policies at local, national and global levels. Ultimately, these efforts should be aimed at health promotion, reducing the burden and costs associated with disease at individual and societal levels, as well as promoting a global healthy life trajectory.

Women constitute a population that demand attention from health care systems and policies [107–109]. In particular, women going through the menopause and beyond — which is a natural and universal process associated with ageing — experience a myriad of biological, psychological and social changes in their life trajectories. This subpopulation of women is showing an increasing interest in their own health and well-being [109]. While for many women, the perimenopause and postmenopause are not necessarily associated with complaints and disease burden, there are others for whom menopausal symptoms are so profoundly disturbing that their quality of life is severely reduced [110], particularly when they have additional risk factors such as obesity or cardiometabolic risk [111]. In addition, they may be concerned by long-term health risks [112, 113].

The impact of menopause-related changes on women's quality of life is strongly linked to personal and sociocultural characteristics, which significantly determine how each woman experiences the perimenopausal transition and the postmenopausal stage. A growing body of evidence shows the influence of various psychosocial factors on women's health during and after menopause, including their perceptions, beliefs, attitudes and lifestyle habits [114, 115]. These factors can in turn influence women’s engagement in health promotion and disease management programmes, the development of support networks, the seeking of professional help and the choice and adherence to therapies such as hormone therapy and other interventions, including lifestyle changes [27]. Therefore, psychosocial factors are important precursors of good health among women in midlife. For this reason, it has been suggested that this life stage may have a positive — rather than negative — impact on women [116]. While the link between psychosocial factors and women’s personal experiences of menopausal symptoms and health-related decision-making has been extensively studied, it remains unclear as to how these factors interact with biomedical variables for influencing the choice of intervention strategies that women use to manage both menopause symptoms and their effects in the short and long term.

All the above demonstrates the importance of implementing exercise programmes for postmenopausal women. It is also crucial to identify and manage the psychosocial and biomedical factors that determine the initiation and adherence to an active lifestyle, beyond the benefits for a woman’s health, well-being and quality of life. Particularly with respect to the determinants of exercise behaviour in middle-aged women, there is limited literature that considers the experiences, needs, resources and opportunities of women in the postmenopausal period. The latter is especially important if one considers the low adherence to the recommended guidelines [10] and the dropout rates (i.e., from partial or temporary abandonment to total and permanent disengagement) among those who have participated in an exercise programme, so that up to half of these women fail to adopt the new habit, particularly as they age or face health conditions [117]. Moreover, gender inequalities should guide practical and policy-oriented efforts to eradicate the differences among women and men in terms of health and lifestyle [107].

The findings of the AHAWOMEN study will offer valuable insights into issues of great significance concerning the health and quality of life of postmenopausal women, specifically in relation to the factors involved in the adoption of healthy behaviours, including exercise. This knowledge will enable a deeper understanding of how to design effective interventions tailored to the needs, opportunities, resources, experiences and circumstances of women in middle age. These interventions should incorporate a range of action strategies, with a particular emphasis on behavioural strategies designed to promote positive health behaviours. Thus, the findings of this research can provide the foundations for developing theory-grounded and evidence-based interventions aimed at promoting an active lifestyle among postmenopausal women. These initiatives have the potential to significantly improve the health and well-being of this population, while preventing disease, premature mortality and unhealthy ageing.

This paper presents the original study protocol. Any significant changes to the protocol will be duly reported to the Institutional Ethics Board, included in the ISRCTN Register and described with transparency in subsequent publications.

